**Methods and analysis:**

RISE is a cluster randomised controlled trial among 12 settlements in Makassar, Indonesia, and 12 in Suva, Fiji. Six settlements in each country have been randomised to receive the intervention at the outset; the remainder will serve as controls and be offered intervention delivery after trial completion. The intervention involves a water-sensitive approach, delivering site-specific, modular, decentralised infrastructure primarily aimed at improving health by decreasing exposure to environmental faecal contamination. Consenting households within each informal settlement site have been enrolled, with longitudinal assessment to involve health and well-being surveys, and human and environmental sampling. Primary outcomes will be evaluated in children under 5 years of age and include prevalence and diversity of gastrointestinal pathogens, abundance and diversity of antimicrobial resistance (AMR) genes in gastrointestinal microorganisms and markers of gastrointestinal inflammation. Diverse secondary outcomes include changes in microbial contamination; abundance and diversity of pathogens and AMR genes in environmental samples; impacts on ecological biodiversity and microclimates; mosquito vector abundance; anthropometric assessments, nutrition markers and systemic inflammation in children; caregiver-reported and self-reported health symptoms and healthcare utilisation; and measures of individual and community psychological, emotional and economic well-being. The study aims to provide proof-of-concept evidence to inform policies on upgrading of informal settlements to improve environments and human health and well-being.

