### Randomisation

Randomisation was performed separately for each city: March 2019 in Makassar and November 2019 in Suva (figure 2). Randomisation occurred following settlement recruitment and completion of 12 months of baseline surveys. Settlements (clusters) have been randomly assigned to either intervention or control groups, with equal numbers in each group. Covariate-constrained randomisation was utilised using the cycrand package in Stata V.15 to achieve balance between the intervention and control groups on key baseline factors determined a priori.

For Makassar, intervention and control groups were first balanced on number of children aged under 5 years (four settlements in each group: ≤10, 11–30 and >30 children) and flood risk (high and low, six settlements in each), producing 90 allocations. Subsequently, the 30 allocations most imbalanced on average asset score were removed, with the score determined from each household’s ownership of selected assets. For Suva, intervention and control groups were first balanced on number of children aged under 5 years (<40 children, eight settlements; >40 children, four settlements) and flood risk and site contamination grouping (two extreme risk, two high risk, and eight medium risk settlements). This resulted in 120 allocations, from which the 30 most imbalanced allocations of asset score were removed, followed by the 30 most imbalanced allocations of average number of children under 5 years. For each of the cities, this resulted in the 60 best balanced allocations being used for the randomisation (total 3600 (60×60) possible allocations for the trial). A randomisation ceremony was held in both cities, where a child from the pilot community selected a ping pong ball from a large glass jar that contained 60 ping pong balls numbered 1–60, representing the 60 determined random allocations that achieved the balance criteria specified above.

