### Sample size

The choice of 12 settlements per city, each of ~55 dwellings with five to six people per dwelling, has been made to balance the need for statistical power with the constraints of construction logistics and cost. Statistical power was calculated using formulae for cluster RCTs with repeated assessments of a cohort^95^ (and confirmed by numerical simulation using generalised linear mixed models) for the three primary health outcomes assessed in children aged under 5 years: (1) prevalence of gastrointestinal pathogens and diversity (number of bacterial, viral and parasitic gastrointestinal pathogens per sample); (2) diversity and abundance of AMR markers and (3) concentration of intestinal inflammation markers. For measures of diversity and abundance of markers of drug resistance in environmental samples, the power calculations assumed the same intracluster correlations as for the health outcomes (see below).

For the health outcomes involving subsampling of an average 30 children under 5 years of age per settlement, there is 80% power to detect, from 6-month postconstruction and beyond, a 40% relative reduction in the prevalence of gastrointestinal pathogens (assuming a baseline prevalence of 25%) and a 31% relative reduction in the average count of enteric pathogens per child (assuming a baseline average count of 1.0 and overdispersion factor of 2; with a baseline of 2.0 the relative reduction is 23%), and at 12 months an absolute difference of 0.30 SDs (and 0.34 SDs for environmental assessments) in the average concentration of intestinal inflammation markers and average number and abundance of AMR markers. These calculations assume intracluster (ie, within-settlement) correlations between: two children within the same time period 0.10^7^; two children in different time periods 0.067; and repeated measurements of the same child 0.10. The relative reduction of 30% has been informed by the findings reported in systematic reviews, which have found reductions of 30%–50% due to water quality interventions.^96 97^

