### Statistical analyses

Analyses will be by intention to treat. Descriptive statistics will report characteristics of settlements and of individuals by randomised arm. Estimation of the effects of the intervention for each outcome will use generalised estimating equations with an exchangeable correlation structure and robust standard errors clustered at settlement level, scaled with a small-sample degrees-of-freedom adjustment.^98^ Data from 6-month, 12-month, 18-month and 24-month follow-up visits will be included in the analysis and the intervention effect estimated for the 6-month follow-up timepoint for prevalence and mean number of gastrointestinal pathogens, and at 12-month follow-up for diversity and abundance of AMR markers and for intestinal inflammation markers. For binary and count outcomes, we will use a logarithmic link to estimate ratios of prevalence and mean counts, respectively; for continuous outcomes, the identity link will be used to estimate differences in means. All models will adjust for the baseline covariates, number of children under 5 years, flood risk category (see Randomisation section) and asset score. To enable temporal adjustment, indicator variables for seasonal patterns (eg, rainy vs dry), local rainfall data for each site and an indicator term for any major flood event at a particular settlement in a particular quarter will be included in the models. For households that drop out of the study, we will employ multiple imputation using imputation models that preserve the hierarchical data structure. Additional sensitivity analyses will exclude households who moved into the settlement postconstruction. There will be no adjustment to the p values for the assessment of multiple primary health outcomes; however, all findings will be fully reported and interpreted based on incremental evidence.

We will explore relationships between environmental changes and health outcomes by modelling health outcomes at 12-month, 18-month and 24-month postconstruction, using changes in environmental measures at 6-month, 12-month or 18-month postconstruction, respectively, as principal covariates. We will estimate these effects using generalised estimating equations with preconstruction health and environmental parameters as baseline covariates aggregated at settlement-level and will include interactions of environmental changes with the intervention for effect-modification assessment, together with adjustment for potential confounders.

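### The primary models omit the settlement's baseline level of the outcome. This costs precision, and adding it restores the stated power only if the effect is also pooled over visits

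*Protocol article*

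**What the plan says.** The Statistical analyses section of the protocol article fits GEE models to the 6-, 12-, 18- and 24-month visits. The pathogen effect is estimated at 6 months; the AMR and inflammation effects are estimated at 12 months. On covariates it says: "All models will adjust for the baseline covariates, number of children under 5 years, flood risk category (see Randomisation section) and asset score". Season, rainfall and flood-event terms are added. The baseline outcome is neither a covariate nor one of the included time points.

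The next paragraph, on exploratory links between environment and health, does use "preconstruction health and environmental parameters as baseline covariates aggregated at settlement-level".

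The Randomisation section says: "Randomisation occurred following settlement recruitment and completion of 12 months of baseline surveys". Allocation was balanced on child numbers, risk grouping and asset score, not on any primary outcome. Table 2 sets stool collection at least twice a year.

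The Sample size section, with "subsampling of an average 30 children under 5 years of age per settlement", states that "there is 80% power to detect, from 6-month postconstruction and beyond, a 40% relative reduction in the prevalence of gastrointestinal pathogens". It gives corresponding figures for counts and for a 0.30 SD difference at 12 months.

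**The concern.** With 12 settlements per arm, the variance of the effect estimate comes mostly from differences between settlements. Some of that variation persists over time: the protocol assumes a correlation of 0.067 between children of one settlement in different periods, against 0.10 in the same period. A settlement's earlier level therefore predicts its later level, and adjusting for it removes variance. The plan expects to have this variable, but names it only for the exploratory question.

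Two things are at stake. One is precision, together with protection against a chance imbalance in the outcome that the constrained randomisation did not address. The other is whether the stated 80% power belongs to the model that the protocol describes.

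**Working it through.** **Inputs.** 24 settlements ("RISE is a cluster randomised controlled trial among 12 settlements in Makassar, Indonesia, and 12 in Suva, Fiji"), allocated "with equal numbers in each group", so K = 12 per arm. m = 30 children per settlement. Correlations from Sample size: 0.10 (two children, same period), 0.067 (two children, different periods), 0.10 (same child over time). Effects: 25% to 15% prevalence; mean count 1.0 to 0.69 and 2.0 to 1.54 with variance twice the mean; 0.30 SD. Alpha is not stated, so two-sided 5% is assumed. The numbers of baseline and follow-up rounds behind the stated power are not given, so several were tried.

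**Variance of a settlement mean (outcome variance set to 1).**
- One period: v = 0.10 + 0.90/30 = 0.130.
- Covariance between periods: c = 0.067 + (0.10 − 0.067)/30 = 0.0681, so r = 0.0681/0.130 = 0.524.
- Average of n periods: [v + (n − 1)c]/n. For two, 0.09905; for four, 0.0836; for unlimited visits, 0.0681.
- After adjusting for baseline: F = (follow-up variance) − c²/(baseline variance).

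**Variance removed.**
- One visit, one round: 0.130 − 0.0681²/0.130 = 0.0943, a cut of 27%. Two rounds: 0.130 − 0.0681²/0.09905 = 0.0832, a cut of 36%.
- Four-visit average, one round: 0.0836 − 0.0357 = 0.0479, a cut of 43%. Two rounds: 0.0836 − 0.0468 = 0.0368, a cut of 56%.

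**Power.** Effective n per arm = 12/F. Power = Φ(difference / standard error − 1.96). The standard error is √(2/n) for the SD effect, √[(0.25×0.75 + 0.15×0.85)/n] for prevalence, and √[2(μ₀ + μ₁)/n] for counts.

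| Follow-up | Baseline rounds | F | 0.30 SD | 25% to 15% | Count 1.0 to 0.69 | Count 2.0 to 1.54 |
|---|---|---|---|---|---|---|
| One visit | 0 | 0.1300 | 53% | 40% | 37% | 38% |
| One visit | 1 | 0.0943 | 67% | 52% | 48% | 50% |
| One visit | 2 | 0.0832 | 72% | 57% | 53% | 55% |
| One visit | 4 | 0.0745 | 77% | 62% | 57% | 59% |
| Four pooled | 0 | 0.0836 | 72% | 57% | 52% | 54% |
| Four pooled | 1 | 0.0479 | 92% | 81% | 76% | 78% |
| Four pooled | 2 | 0.0368 | 97% | 90% | 86% | 88% |
| Unlimited | 0 | 0.0681 | 80% | 66% | 61% | 63% |

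A pooled null variance lowers the prevalence figures by up to about one point. A t reference with 22 df lowers power somewhat: for prevalence with four visits pooled it gives 53% without baseline and 77% with one round.

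**Reproducing the stated 80%.** The prevalence figure is matched by one baseline round and four pooled visits (80.1% with the pooled null variance). The 0.30 SD figure is matched by one baseline round and two visits (79.7%, t with 22 df). No single configuration tried matches every stated effect. Without baseline, prevalence and counts stay below 80% even with unlimited visits. A one-sided 5% test does not change this: with four visits pooled and no baseline it gives about 69% for prevalence and 65–67% for counts.

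**If correlation decays.** Suppose the baseline-to-follow-up covariance falls to 0.04 over the design and build period (an assumption). With two rounds, 0.04²/0.09905 = 0.0162 is removed. One visit goes from 0.130 to 0.1138 (12%) and the four-visit average from 0.0836 to 0.0674 (19%). Prevalence power then rises only from 40% to 45%, and from 57% to 66%.

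**The case against.** A reader might infer that the missing covariate invalidates the primary analysis. It does not. Randomisation keeps the comparison unbiased, and chance imbalance is reflected in the settlement-clustered, small-sample-adjusted standard errors. The loss is precision.

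A reader might also infer that adding the covariate restores the planned power. The Statistical analyses section ties the pathogen effect to 6 months. For an effect at one visit, even four baseline rounds give 62% for prevalence and 57–59% for counts. For 0.30 SD at 12 months they give 77%. So the shortfall is partly a matter of which effect is estimated. The Sample size wording, which speaks of 6 months and beyond, leaves room for pooling, but the analysis text does not state it.

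Other cautions stand in part:
- The percentage gains are on the optimistic side. The roughly 5-year timeline puts a long gap between baseline and follow-up. Flood risk and asset score may already absorb some between-settlement variance, although the protocol gives no figure for this.
- Small settlements gain less. At 10 children, one round cuts single-visit variance by [(0.067 + 0.033/10)/(0.10 + 0.90/10)]² = (0.0703/0.190)² = 14%, against 27% at 30. The Randomisation section puts four Makassar settlements at 10 children or fewer.
- Baseline stool results are inferred. The Randomisation section speaks of surveys, and Table 2 gives a minimum frequency, not rounds obtained. The limitations section warns that assays may change. The planned preconstruction health covariates nevertheless imply that such data are expected.
- An analysis plan that is not shown could add the term. But the article says what all models adjust for, and the three items listed are randomisation factors. Reading an unnamed baseline outcome into that list is strained.

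**Conclusion.** The point holds as a matter of precision, together with a power statement that does not match the described model. Under the protocol's correlations, omitting the settlement baseline forgoes a variance reduction of about 27% (one visit) or 43% (four-visit average) with one round, and 36% or 56% with two. Under the decay assumption, two rounds still give about 12% and 19%.

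For prevalence and counts, no configuration without baseline reaches 80%: the ceilings are about 66% and 61–63%. Under undiminished correlations, one round with four visits pooled gives about 80% for prevalence and 76–78% for counts; two rounds take both above 80%. Baseline adjustment is therefore needed for the stated power but not sufficient for it.

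These results rest on two-sided 5%, 30 children in every settlement, baseline stool data being available, and no variance already explained by the three named covariates.

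**What to change.** Prespecify the settlement-level pre-randomisation mean of the same outcome as a covariate in each primary model. Do the same in secondary models where the same measure exists at baseline and follow-up; this excludes, for example, rodent trapping, which is baseline only. Use the settlement mean because many children sampled at follow-up will not have been sampled at baseline.

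For prevalence and counts, choose a form that is defined at zero: the untransformed mean, an empirical logit, log(x + constant), or a shrunken settlement estimate. A plain log fails when a small settlement has no positives. At 25% prevalence and correlation 0.10 (beta-binomial), that happens in one round with probability about 14% for 10 children and 31% for 5.

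State whether each primary effect is visit-specific or pooled over visits, and restate power for that estimand, with the assumed alpha, number of rounds and correlation across the build period.

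The cost is one degree of freedom per model, out of 24 settlements, and no new data. The change should be recorded before outcomes are compared by arm, so that it cannot look data-driven.

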## Study methods and analysis

### Overview of the study design and timeline

To evaluate the RISE intervention, we are conducting a cluster RCT involving 12 informal settlements in Suva, Fiji, and 12 in Makassar, Indonesia, with clustering at the settlement level. In each country, half of the sites have been randomised as intervention communities and will receive an early upgrade. The remaining communities will serve as controls and will receive only standard, basic hygiene and sanitation messages. Monitoring and assessment will be conducted in all settlements over an approximate 5-year timeline, which will include baseline data collection, the design and build implementation phase of the project, and 2 years of post-build monitoring (figure 2). After completion of the study, the intervention will be implemented in the 12 control settlements.

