**Secondary outcomes**				
***Physical Health Measures***				
Blood collection for haemoglobin and blood inflammatory markers, children <5 years				X
Anthropometry measures (length-for-age, weight-for-age and weight-for-length z-scores) measure, children <5 years of age				X

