***Surveys: Household and community demographic, health and well-being***				
Household members and demographics				X
Household member behaviours and exposures			X	
Access to sanitation, water and hygiene facilities*				*
Caregiver-reported acute symptoms (diarrhoea, respiratory infections and febrile illness), children <5 years of age		X		
Healthcare system utilisation, children <5 years of age		X		
Self-reported or caregiver-reported acute symptoms, healthcare system utilisation and subjective general health (5-point rating scale) among adults and children 5–15 years			X	
Caregiver assessed quality of life (Paediatric Quality of Life Inventory, PedsQL, emotional functioning dimension), children 5–15 years			X	
Self-reported life satisfaction—multiple domains (10-point rating scale), adults			X	
Centre for Epidemiologic Studies Depression Scale (CES-D-10), adults				X
Self-reported major adverse life events, adults			X	
Time-use surveys, children 5–15 years and adults*				*
Housing tenure+ and collective efficacy (Likert 5-point scales)				X
Indicators of household assets and expenditure*				*
Intermittent qualitative surveys and focus groups	NA			

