### Secondary outcomes

#### Human health secondary outcomes

Secondary health outcomes include caregiver-reported and self-reported acute symptoms, healthcare utilisation, inflammatory markers in blood, haemoglobin levels and anthropometry measures. Caregiver-reported and self-reported symptoms will be collected via standardised questionnaires throughout the trial, including the presence of diarrhoea, respiratory and undifferentiated febrile illness over the 7 days prior to the survey visit.^72^ Symptoms will be assessed quarterly in children under the age of 5 years and every 6 months in children between 5 and 15 years of age and adults. In all cases, diarrhoea is defined as ≥3 loose or watery stools in a 24-hour period. Healthcare utilisation (visitation to healthcare provider, hospitalisation, antibiotic use) by children under 5 years of age within the 3 months prior to the visit will be surveyed quarterly; for children 5–15 years of age and adults, surveys will be 6 monthly.

Blood from children under 5 years of age will be taken annually by venipuncture. Haemoglobin levels will be measured in the field using a point-of-care device. Plasma and whole blood will be stored for further analyses, which will include markers of nutrition and inflammation. To obtain length-for-age, weight-for-age and weight-for-length z-scores in children under 5 years of age, trained staff will follow standard procedures for anthropometric measurements.^73^ Pairs of trained anthropometrists will measure standing (in children between 2 and 5 years of age) or recumbent (less than 2 years of age) length (accurate to 0.1 cm) and weight without clothing (accurate to 0.1 kg) in triplicate. In both cases, the median of the three measurements will be used in the analysis.^74^

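### The terms named for all models include no child age at sampling, which gives up a small amount of precision for any primary outcome that varies with age

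*Protocol article*

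**What the plan says.** Under Statistical analyses, the protocol article gives one covariate sentence for everything: "All models will adjust for the baseline covariates, number of children under 5 years, flood risk category", together with asset score. For temporal adjustment it adds "indicator variables for seasonal patterns (eg, rainy vs dry), local rainfall data for each site and an indicator term for any major flood event". The count of under-fives is a settlement characteristic used in the constrained randomisation, not a child's age. Asset score is built from household assets. An open-ended allowance for adjusting for confounders appears only in the next paragraph, for the exploratory models linking environmental change to health.

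The primary outcomes (pathogens, resistance genes and inflammation markers) all come from stool of children under 5, and monitoring runs "over an approximate 5-year timeline". Age is available from two sources. Human health secondary outcomes says that staff will measure children "To obtain length-for-age, weight-for-age and weight-for-length z-scores in children under 5 years of age", and length-for-age and weight-for-age cannot be computed without age. Table 2 also lists "Household members and demographics" as an annual survey item.

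Inference uses generalised estimating equations with "robust standard errors clustered at settlement level, scaled with a small-sample degrees-of-freedom adjustment".

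**The concern.** The outcomes span birth to 5 years, and over roughly five years of monitoring children enter and leave that band, so the age mix of sampled children can shift between settlements and visits. The randomisation balanced the number of under-fives, flood risk (with site contamination in Suva) and assets, but not ages. If an outcome varies with age, an age term would remove part of the child-to-child variation from the arm comparison.

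The number of settlements was limited by construction logistics and cost, so precision cannot easily be bought another way. Age is also an unusually safe covariate: the intervention cannot change it, and as a child-level term it uses almost none of the settlement-level degrees of freedom, which matters with 24 clusters.

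**Working it through.** **Inputs from the protocol article (Sample size; Randomisation).** 12 settlements per arm; an average of 30 children sampled per settlement; correlation 0.10 for two children in the same period, 0.067 in different periods, and 0.10 for the same child; 80% power for a fall in pathogen prevalence from 25% to 15% (40% relative) and for 0.30 SD at 12 months. Four Makassar settlements have 10 or fewer under-fives.

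**Assumptions.** Two-sided 5% level. R², the share of child-level variance explained by age, is 5–20%. The size m = 8 is an illustration for the smallest Makassar band. Scaling child-level variance by (1 − R²) is a linear-model approximation for the binary and count outcomes.

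**1. The plan's own power.** The number of survey waves behind the 80% is not stated. Let d = 0.10 + 0.90/30 = 0.130 be the variance of a settlement mean in one wave. Reading the same-child 0.10 as a total correlation, let o = 0.067 + 0.033/30 = 0.0681 be the covariance between waves. With f follow-up waves and one baseline wave used as a covariate, v = [d + (f − 1)o]/f − o²/d.

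- f = 4: v = 0.0836 − 0.0357 = 0.0479. Prevalence: SE = √[(0.1875 + 0.1275) × 0.0479/12] = 0.0355; 0.10/0.0355 = 2.82; power 80.5% (normal).
- f = 2: v = 0.0991 − 0.0357 = 0.0634. Continuous: SE = √(2 × 0.0634/12) = 0.103; 0.30/0.103 = 2.92; power 79.6% (t, 22 df).

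Each figure can be matched, but by a different layout; no single layout tried gives both. The stated power is neither confirmed nor refuted, so the gains below start from a nominal 80%.

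**2. Child-level share of a one-wave settlement mean.**

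- m = 30: 0.030/0.130 = 23%.
- m = 8: 0.1125/0.2125 = 53%.

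**3. Variance removed by age**, with R² × (0.90/m)/(0.10 + 0.90/m):

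| m | R² = 5% | R² = 20% |
|---|---|---|
| 30 | 1.2% | 4.6% |
| 8 | 2.6% | 10.6% |

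**4. Power at m = 30.** Multiply 0.90 and 0.033 in step 1 by (1 − R²), recompute v, and take power = Φ(2.80/√(v_new/v_old) − 1.96).

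| Layout | Variance cut (R² 5%, 20%) | Power (R² 5%, 20%) |
|---|---|---|
| One follow-up, no baseline | 1.2%, 4.6% | 80.5%, 81.8% |
| Four follow-ups, no baseline | 0.5%, 2.0% | 80.2%, 80.8% |
| One baseline, four follow-ups | 1.6%, 6.6% | 80.6%, 82.6% |
| One baseline, two follow-ups | 1.8%, 7.3% | 80.7%, 82.9% |

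The last two rows assume adjustment for the baseline outcome, which the covariate sentence does not name. Over these layouts a detectable 0.30 SD becomes 0.299 to 0.289 SD.

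**5. Chance age imbalance.** If ages are uniform over 0–60 months (SD 60/√12 = 17.3) and do not cluster by settlement, the SD of the arm difference in mean age is 17.3 × √(2/360) = 1.3 months. If age explains 10% of the outcome variance, that moves an estimate by about √0.10 × √(2/360) = 0.024 SD, against a detectable 0.30 SD.

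**The case against.** The case for leaving this alone is strong in several respects.

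- A reader might infer that the covariate list is closed. The text does not say so. It names the randomisation factors and temporal terms and excludes nothing, and an analysis plan that is not shown could add age without contradiction. This stands. Even so, the sentence governs all models and names no child-level term, so adding age would be a specific change to a stated model.
- A reader might infer bias from uneven age mix. The design does not support that. Randomisation makes such imbalance a matter of chance, and the settlement-clustered errors already carry it; step 5 shows how small it is likely to be.
- A reader might infer that every primary estimate suffers. The article gives no age gradient for any primary outcome and no age distribution by settlement or visit. The loss applies only where an outcome varies with age, and R² is an assumption throughout.
- The small-settlement figures should not be generalised. Four of the 24 settlements are in the band of 10 or fewer, and the planning average is 30.

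**Conclusion.** This is a minor point of efficiency, and the primary analysis is valid as planned. For a primary outcome that varies with age, the named terms leave a modest amount of removable noise. At the planned 30 children per settlement the gain is about 0.2 to 3 power points, with its upper end reached only if age explains about 20% of child-level variance and the baseline outcome is also used. The limit comes from the trial's own correlation of 0.10: at that value child-level variation is under a quarter of the variance of a settlement mean. The gain would be larger if mean age itself differed between settlements, on which the article is silent.

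**What to change.** Prespecify child age at the time of sampling as a covariate in the primary models for the under-five stool outcomes, for example in bands of 0–11, 12–23 and 24–59 months, or as linear plus quadratic terms. If the analysis plan already does this, the article's sentence only needs to be read alongside it. Settle the form before outcome data by arm are seen, because a later addition would look data-driven.

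The cost is one line of text and one to three child-level parameters, with no new data collection. Entered without an interaction with arm, an age term leaves the target of estimation unchanged under both the logarithmic and the identity link.
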